#### Statistical control for confounding factors

2.12.5

Potential confounders, including age, sex, PSD duration, baseline NIHSS and FOIS scores, stroke subtype, comorbidities (hypertension, diabetes), total treatment expectation scores, and the Deqi Index (DQI), will be accounted for in the analyses. For primary and secondary efficacy outcomes, repeated-measures mixed-effects models or multiple linear regression will be employed. Stroke subtypes will be examined using stratified analysis, while comorbidities will be assessed via sensitivity analyses.

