### Sample size, randomization, and blinding

2.7

The primary efficacy outcome is the FOIS score. As neither our team nor previous studies have used this measure to assess acupuncture efficacy for post-stroke dysphagia, it is not possible to determine an appropriate effect size from existing data. A review of similar studies has revealed that after 4 weeks, the FOIS score difference from baseline was 1.31 (rehabilitation training group) vs. 0.31 (sham training group), with a standard deviation of 1.09 (16). This value will be used as the expected effect size for this trial, and sample size calculations will be conducted based on a superiority trial design (17). These parameters (μA = 1.31, μB = 0.31, σ = 1.09, α = 0.05, power = 0.8, δ = 0.39) were applied in a superiority design with 1:1 allocation. After calculation, nA = nB = 40. Considering a 20% dropout rate, this study is expected to enroll 100 patients.

Randomization will use computer-generated numbers to allocate patients equally to acupuncture or rehabilitation groups. A stratified block randomization design will be employed. An independent statistician will generate all random sequences in SPSS 25.0, with study center and baseline FOIS as stratification factors, block lengths of 4 and 6 randomly interleaved, and the seed number set to 20240420. Allocation concealment will be implemented through sequentially numbered, opaque, sealed envelopes kept by a research coordinator who has no conflicts of interest with the study team. After participants have completed baseline assessments and provided written informed consent, the responsible physician will open the corresponding envelope on-site to reveal the allocation. The statistician generating the random sequence will operate independently of the coordinator handling allocation concealment. Neither patients nor physicians will know the allocation in advance. All participants will be followed for 90 days.

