### Evaluation schedule

2.10

FOIS, NIHSS, SWAL-QOL, PAS, and YPR-SRS will be assessed at baseline (pre-treatment), 15 and 30 days after treatment initiation, and 30 and 60 days post-treatment completion. Additionally, fMRI-derived ReHo and ALFF metrics, sEMG evaluations, and PRO scores will be obtained at baseline and at 15 and 30 days following treatment initiation. The study timeline for enrollment, intervention, and assessment is detailed in Table 4. All dropouts and their respective reasons will be systematically documented in the case report forms (CRFs).

**TABLE 4 T4:** Study assessment schedule.

Times outcomes	Before treatment	Treatment				Follow-up	
	Day 3–0	Week 1–2	(Day 15)	Week 2–4	(Day 30)	Day 60	Day 90

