#### Functional imaging evaluation indicators

2.12.1

Statistical analysis is performed using the DPABI V5.1^3^ software package. Whole-Brain Analysis: Paired *t*-tests will be used to compare pre- and post-intervention ALFF, fALFF, ReHo, and FC values within each group (acupuncture and rehabilitation training), as well as between groups after intervention. Based on prior evidence indicating direction-specific neuromodulation by acupuncture in swallowing networks (47, 48), the resulting statistical maps will be corrected using one-tailed Gaussian random field theory (voxel *p* < 0.01, cluster *p* < 0.05). ROI Analysis: Mean ReHo and ALFF values will be extracted from each ROI and analyzed using repeated-measures ANOVA to assess within-group changes over time and between-group differences.

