#### Analysis adjusting for treatment expectations

2.12.3

For the primary efficacy outcome (FOIS) and key secondary subjective measures (SWAL-QOL, PRO), analysis of covariance (ANCOVA) or mixed-effects models will be employed, with the total baseline treatment expectation score included as a covariate to control for its potential influence on treatment outcomes.

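### The covariates named for the secondary outcomes include baseline FOIS and NIHSS but not each outcome's own baseline, so own-baseline adjustment of SWAL-QOL, PRO, YPR-SRS and sEMG is not fixed

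*Protocol article*

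**What the plan says.** Section 2.12.5 lists the adjustment variables: "Potential confounders, including age, sex, PSD duration, baseline NIHSS and FOIS scores, stroke subtype, comorbidities (hypertension, diabetes), total treatment expectation scores", followed by the Deqi index. The same section gives the models: "For primary and secondary efficacy outcomes, repeated-measures mixed-effects models or multiple linear regression will be employed". It does not choose between the two, and it does not say whether the baseline visit enters as a response, as a covariate or not at all.

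Section 2.12.3 provides for ANCOVA or mixed-effects models for FOIS, SWAL-QOL and PRO, the latter two described as key secondary measures. The one covariate it names is expectation: "with the total baseline treatment expectation score included as a covariate to control for its potential influence on treatment outcomes".

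The baselines are available. Section 2.10 states "FOIS, NIHSS, SWAL-QOL, PAS, and YPR-SRS will be assessed at baseline (pre-treatment), 15 and 30 days after treatment initiation", and also "fMRI-derived ReHo and ALFF metrics, sEMG evaluations, and PRO scores will be obtained at baseline and at 15 and 30 days following treatment initiation". Table 4 agrees.

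Randomisation is stratified "with study center and baseline FOIS as stratification factors" (section 2.7), so the design does not directly balance the baseline of any secondary scale.

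**The concern.** The baseline value of a scale is usually among the best predictors of its later value. The article lists its covariates item by item and carries baseline FOIS and NIHSS into the models for other scales. It does not name the corresponding baseline for SWAL-QOL, PRO, YPR-SRS or sEMG.

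An analyst who fits the regression or ANCOVA with only the named covariates would therefore give up precision. Any chance difference between the arms at baseline on the analysed scale would also stay in the estimate, except for the part explained by FOIS, NIHSS and the other covariates. With about 40 completers per arm such differences are not rare. The choice of how baseline enters would also be left open until analysis.

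**Working it through.** **1. The plan's own figure.** The article states no power for any secondary outcome. The only figure is the FOIS sample size, from "μA = 1.31, μB = 0.31, σ = 1.09, α = 0.05, power = 0.8, δ = 0.39". With an effective difference of 1.31 − 0.31 − 0.39 = 0.61 and one-sided α = 0.05:

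n per arm = 2 × 1.09² × (1.645 + 0.842)² / 0.61² = 39.5, rounded up to 40.

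Allowing for 20% dropout, 40 / 0.8 = 50 per arm, or 100 in total. This reproduces the plan and does not depend on the present point. It supplies the 40 per arm used below.

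**2. Size of chance imbalance.** One standard error of the baseline difference is √(2/40) = 0.22 SD with 40 per arm, and √(2/50) = 0.20 SD with 50 per arm.

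**3. Precision gained, with baseline FOIS already in the model.** The documents give none of the correlations, so all are assumed:
- ρ: outcome with its own baseline.
- a: outcome with baseline FOIS.
- b: own baseline with baseline FOIS.

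R² with both baselines = (ρ² + a² − 2ρab) / (1 − b²).

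Residual variance ratio = (1 − R²) / (1 − a²).

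Power after the change = Φ((1.960 + 0.842)/√ratio − 1.960). This takes two-sided α = 0.05 and, as an assumption, 80% power before the change. A noncentral t calculation with 78 degrees of freedom gives the same percentages to within rounding.

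Example for ρ = 0.5, a = 0.3, b = 0.4: R² = (0.25 + 0.09 − 0.12)/0.84 = 0.262, and the ratio is 0.738/0.91 = 0.81.

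| ρ | FOIS not predictive (a = b = 0) | a = 0.3, b = 0.4 | a = 0.4, b = 0.5 |
|---|---|---|---|
| 0.3 | 0.91, power 84% | 0.96, power 82% | 0.98, power 81% |
| 0.5 | 0.75, power 90% | 0.81, power 88% | 0.86, power 86% |
| 0.7 | 0.51, power 98% | 0.56, power 96% | 0.60, power 95% |

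The last two columns fit this plan, because baseline FOIS is a named covariate.

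**4. Simulation.** 4,000 runs, 40 per arm, a = 0.3, b = 0.4, no true effect. All models include baseline FOIS. Entries are standard errors of the arm effect in SD units.

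| ρ | Post-treatment value only | Own baseline added | Change from baseline |
|---|---|---|---|
| 0.3 | 0.215 | 0.213 | 0.269 |
| 0.5 | 0.217 | 0.197 | 0.227 |
| 0.7 | 0.215 | 0.162 | 0.175 |

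Relative to the change contrast, the own-baseline covariate reduces variance by 1 − (0.213/0.269)² = 37% at ρ = 0.3, 1 − (0.197/0.227)² = 25% at 0.5, and 1 − (0.162/0.175)² = 14% at 0.7.

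Averaged over all runs, each of the three estimators was within 0.005 SD of zero, that is, unbiased. In the runs where the baseline difference exceeded 0.2 SD, the mean errors at ρ = 0.3, 0.5 and 0.7 were:
- post-treatment value only: 0.07, 0.12 and 0.18 SD;
- change from baseline: −0.21, −0.16 and −0.09 SD;
- own baseline as covariate: within 0.01 SD of zero.

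**The case against.** The strongest reply is that the article is silent here rather than wrong. The list in 2.12.5 opens with the word *including*, so it is illustrative, and 2.12.3 does not call expectation the only covariate. Outcome-by-outcome model statements are commonly left to a full protocol or analysis plan. This stands in part: a reader might infer that the secondary models omit the own baseline, and the documents do not support that, because nothing excludes it. What remains is that the article does specify adjustment in detail, and what it specifies can be improved.

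Second, a repeated-measures mixed model is permitted and would use the own baseline if that visit is a response. For the imaging regions of interest, section 2.12.1 already has the values "analyzed using repeated-measures ANOVA to assess within-group changes over time and between-group differences", which may include the baseline scan. This also stands, but an ordinary arm-by-time contrast with baseline as an unconstrained response is a difference in change. In the simulation that was less precise than conditioning on baseline at every correlation tried.

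Third, a reader might infer that the arm effect is biased. It is not: under randomisation imbalance is a matter of chance, and the harm is lost precision and error conditional on the imbalance that occurs. Stratifying on baseline FOIS also limits imbalance in whatever these scales share with FOIS.

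Fourth, the size should not be overstated. A gain of about 4 power points at ρ = 0.3 holds only if no other covariate predicts the outcome. With baseline FOIS in the model it is about 1 to 2 points. The other listed covariates may absorb more of the gain at any ρ.

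**Conclusion.** The point holds as a gap in the stated adjustment that is cheap to close, not as a demonstrated error. Sections 2.12.3 and 2.12.5 do not fix own-baseline adjustment for SWAL-QOL, PRO, YPR-SRS or sEMG, and a regression or ANCOVA with only the named covariates would lose precision.

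The loss depends on a correlation that the documents do not give. With baseline FOIS in the model it is negligible at ρ = 0.3 and worth recovering at 0.5. At 0.7 it is large against a post-only model, but only about 14% of variance against a change contrast. The 80% reference power is an assumption too, since the plan claims none for these outcomes.

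FOIS and NIHSS already have their own baselines named, so the primary analysis and NIHSS are untouched, as is the sample size.

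**What to change.** State in 2.12.3 and 2.12.5 that each continuous or scale secondary outcome is adjusted for its own baseline value, in addition to baseline FOIS, with only post-baseline visits as responses. This applies to SWAL-QOL, PRO, YPR-SRS and the numeric sEMG measures such as duration and amplitude. It does not apply to sEMG waveform patterns, for which a baseline value as covariate is not defined. An acceptable alternative is to model baseline as a response with arm means constrained equal at that visit. Name one of the two before the data are analysed.

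The cost is a sentence in each section and one degree of freedom per model. No new data are needed.

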### Recruitment of study participants

2.6

The study will be conducted at two hospitals of Hunan University of Traditional Chinese Medicine (First and Second Affiliated Hospitals), with the Second Affiliated Hospital leading study design and implementation. PSD participants will be recruited from hospital wards/clinics (April 2024-June 2025), while healthy controls will be enrolled from the community during the same period.

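### Study center is a stratification factor but is named in no efficacy or imaging analysis; adding it is a minor, nearly free gain in precision

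*Protocol article*

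**What the plan says.** Section 2.7 of the protocol article describes stratified block randomisation "with study center and baseline FOIS as stratification factors, block lengths of 4 and 6 randomly interleaved". There are two centers, according to section 2.6: "The study will be conducted at two hospitals of Hunan University of Traditional Chinese Medicine (First and Second Affiliated Hospitals").

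The analysis sections then name these terms:

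- **Section 2.12.5**, for the primary and secondary efficacy outcomes: "Potential confounders, including age, sex, PSD duration, baseline NIHSS and FOIS scores, stroke subtype, comorbidities (hypertension, diabetes"), followed by the expectation score and the deqi index. Baseline FOIS is on the list and center is not. The models are repeated-measures mixed models or multiple linear regression, and no center effect, fixed or random, is mentioned.
- **Section 2.12.3**, for FOIS, SWAL-QOL and PRO: ANCOVA or a mixed model "with the total baseline treatment expectation score included as a covariate". No other covariate is named there.
- **Section 2.12.4**: the deqi index and time.
- **Section 2.12.1**: paired t-tests for the whole-brain maps; for the regions of interest, "Mean ReHo and ALFF values will be extracted from each ROI and analyzed using repeated-measures ANOVA". No center term.
- **Section 2.12.2**: chi-square, Fisher and Mann-Whitney tests, none of them stratified.
- **Section 2.12.6 and Table 5**: center is not among the subgroups.

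**The concern.** Stratifying on a factor balances it between the arms. If the factor predicts outcome, this balance lowers the true sampling variance of the treatment difference. A model that leaves the factor out keeps its variance in the residual, so the reported standard error does not reflect the gain. Confidence intervals are then too wide, the test runs below its nominal level, and some power is given away. The usual remedy is to carry the randomisation strata into the model.

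The analysis sections do this for baseline FOIS, through section 2.12.5, but nowhere for center. The stake is precision, in a trial planned at about 80% power whose authors list small sample size as a limitation.

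**Working it through.** **Inputs from the document.** Section 2.7 gives "μA = 1.31, μB = 0.31, σ = 1.09, α = 0.05, power = 0.8, δ = 0.39"; these "were applied in a superiority design with 1:1 allocation". The result is "After calculation, nA = nB = 40", raised to 100 patients in total for 20% dropout. Two centers (section 2.6).

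**Reproducing the sample size.** Difference beyond the margin = 1.31 − 0.31 − 0.39 = 0.61.

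n per arm = 2σ²(z_α + z_β)² / 0.61² = 2 × 1.09² × (1.645 + 0.842)² / 0.61² = 39.5, so 40. Then 40 / 0.8 = 50 per arm, or 100 in total.

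The stated figures reproduce with a one-sided α of 0.05, which is used below. The article does not state the sidedness; two-sided 0.05 with the same margin would need 51 per arm. That is a separate matter.

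**Assumed, because the document gives no figure.** D is the difference in mean FOIS change between the centers, taken from 0 to 1.0 point. p is one center's share of patients, 0.5 or 0.7. The SD of 1.09 is taken as the total SD, center included.

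**Formulas.**

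- Within-center SD: σ_w = √(1.09² − p(1 − p)D²)
- SE reported without center: 1.09 × √(2/40) = 0.244
- SE with center: σ_w × √(2/40)
- Power with center: Φ(0.61 / SE_with − 1.645)
- Power without center: Φ(0.61 / SE_with − 1.645 × 1.09/σ_w), because stratification has already reduced the true variance while the test still uses the larger SE
- Actual one-sided type I error without center: 1 − Φ(1.645 × 1.09/σ_w)

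Example, D = 1.0 and p = 0.5: σ_w = √(1.1881 − 0.25) = 0.969, and 1.09 / 0.969 = 1.125.

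| D (p = 0.5) | SE without | SE with | SE excess | Power without | Power with | Type I error without |
|---|---|---|---|---|---|---|
| 0 | 0.244 | 0.244 | 0% | 80.5% | 80.5% | 5.0% |
| 0.25 | 0.244 | 0.242 | 0.7% | 80.6% | 80.9% | 4.9% |
| 0.5 | 0.244 | 0.237 | 2.7% | 81.1% | 82.3% | 4.6% |
| 0.75 | 0.244 | 0.229 | 6.5% | 82.0% | 84.6% | 4.0% |
| 1.0 | 0.244 | 0.217 | 12.5% | 83.3% | 87.9% | 3.2% |

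The largest power loss is 87.9 − 83.3 = 4.6 points. With a 70:30 split and D = 1.0, the SE excess is 10.2% and power is 82.8% against 86.7%, a loss of 3.9 points.

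**Simulation check.** 80 completers, two centers by three FOIS levels as strata, blocks of 4 and 6, linear model with baseline FOIS, with and without center, 6,000 runs per case.

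- Power without and with center: 80.3% and 81.9% at D = 0.5; 82.7% and 87.9% at D = 1.0.
- One-sided type I error without center: 4.7% at D = 0.5; 3.9% at D = 1.0.

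The direction and the power figures agree with the formulas. At D = 1.0 the simulated 3.9% lies above the 3.2% from the formula. The formula assumes exact balance within centers, which incomplete blocks do not give, so it overstates the conservatism somewhat. Part of the gap is simulation noise: the Monte Carlo standard error near 5% is √(0.05 × 0.95 / 6000) = 0.28 points, and the model with center, which should run at 5%, gave 5.75% in the same runs.

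**The case against.** The strongest reply is that this rests on silence in a condensed article. The list in section 2.12.5 is introduced as examples of potential confounders, so it is open. Nothing says that center will be left out, and a separate analysis plan could add it. What remains is that the article does publish a detailed list, and that list carries one of the two stratification factors and not the other. Asking for the second is fair; calling its absence a flaw in validity would not be.

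Four stronger readings are tempting, and the documents do not support them.

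- **That precision is in fact lost.** This requires center to predict outcome, and no figure is given. The sites are two affiliated hospitals of one university, and section 2.11 requires a common treatment protocol at all centers. A difference of 1.0 point would equal the entire treatment difference assumed in section 2.7, so the top of the range is an outer bound rather than an expectation.
- **That baseline FOIS is omitted too.** Section 2.12.5 lists it for primary and secondary outcomes. Section 2.12.3 explains how the expectation score enters; it does not say that this is the only covariate.
- **That all the imaging tests are affected.** In a within-patient before-and-after comparison, an additive center effect cancels. The point bears only on between-group comparisons.
- **That the sites are known to differ in scanners.** The Discussion mentions equipment variability among the challenges that a two-center design keeps small. Which scanners are used, and whether both sites scan, is not stated.

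**Conclusion.** The point holds as a minor one. Randomisation is stratified by center, and no efficacy or imaging analysis names center. With 40 patients per arm, one-sided α of 0.05, total SD 1.09 and an even split, leaving center out overstates the SE by 0 to about 12.5% and costs 0 to about 5 percentage points of power as the assumed center difference goes from 0 to 1.0 FOIS point. Up to 0.5 point, the excess is at most 2.7% and the power loss at most 1.2 points (82.3 − 81.1).

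A reader might infer that the omission inflates the type I error or biases the treatment estimate. It does neither: the test errs on the conservative side, and what is lost is mainly reported precision.

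**What to change.** State in section 2.12 that:

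- the primary between-arm FOIS model includes center, as a fixed effect with two levels, and baseline FOIS;
- the between-arm models for secondary outcomes include center and the baseline value of the outcome;
- the between-group whole-brain and region-of-interest imaging comparisons include center. Within-patient paired tests do not need it.

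A fixed effect is preferable to a random one, because a variance estimated from two centers would be very poor.

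The cost is a sentence or two of wording and one degree of freedom per model for center. No change to sample size, randomisation or data collection is needed.

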**FIGURE 2 F2:**
[figure not shown]
Location of acupuncture points (Source: Atlas of meridians and acupuncture points by JiuDaifu).

**TABLE 2 T2:** Anatomical location of selected acupoints.

Acupoints	Location
GB20 (Fengchi)	In the posterior region of the neck, under the occiput, in the depression between the upper part of the sternocleidomastoid muscle and the upper part of the trapezius muscle.
GB12 (Wangu)	On the neck, at the posterior and inferior depression of the mastoid process behind the ear.
TE17 (Yifeng)	On the neck, behind the earlobe, at the anterior and inferior depression of the mastoid process.
CV23 (Lianquan)	In the anterior region of the neck, on the anterior median line, above the laryngeal prominence, and in the depression of the upper edge of the hyoid bone.

Patients will lie in a supine position. GB20 (Fengchi) needles will be bilaterally inserted at a 30° inferior angle toward the thyroid cartilage to a depth of 2.5–3.0 cun (≈65–75 mm). Small-amplitude, high-frequency twisting manipulation will be applied for 1 min to achieve strong stimulation, targeting a throat numbness/swelling sensation called “deqi.” GB12 (Wangu) and TE17 (Yifeng) will be needled with the same depth, angle, and technique as GB20. CV23 (Lianquan) will be inserted to 1.0–1.5 cun (≈25–40 mm) with lifting-thrusting manipulation. All needles will be retained for 30 min. Participants will receive three sessions per week for four consecutive weeks.

Deqi will be assessed subjectively using the Chinese version of the Massachusetts General Hospital Acupuncture Sensation Scale (c-MASS) (20), which evaluates 12 distinct sensations to quantify deqi intensity and quality. Participants will self-complete the c-MASS within 30 s after each needle manipulation. In accordance with prior domestic research (21), “adequate deqi” will be defined as a total c-MASS score ≥ 4, accompanied by at least two typical sensations (soreness, numbness, fullness, or heaviness) each rated ≥ 3. Cases not fulfilling both criteria will be classified as “inadequate deqi.” The Deqi Quality Index (DQI) for each participant will be calculated as the mean of the total c-MASS scores recorded at three time points: initiation of intervention, 15 and 30 min.

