#### Analysis of Deqi

2.12.4

Group comparisons will be performed based on the binary classification of “adequate” versus “inadequate” deqi, with the Deqi Quality Index (DQI) included as a covariate in an analysis of covariance (ANCOVA) to assess therapeutic effects. Additionally, a linear mixed-effects model will be employed to examine the significance of the DQI × time interaction.

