#### Predefined subgroup analysis

2.12.6

Subgroup analyses will be prespecified in accordance with subgroup data reporting guidelines (49), with details provided in Table 5 (50–54). The results, which will be Bonferroni-corrected for multiple comparisons, will be reported as secondary exploratory outcomes. Treatment effect differences between the acupuncture and rehabilitation control groups across subgroups will be presented using forest plots.

**TABLE 5 T5:** Predefined subgroup categories and rationale.

Subgroup category	Stratification basis (determined at baseline)	Theoretical rationale
Baseline FOIS score subgroup	Low-level group (FOIS = 2), Medium-level group (FOIS = 3–4)	The severity of baseline swallowing function may affect intervention response. Patients with FOIS = 2 and those with FOIS = 3–4 have different therapeutic goals (e.g., prioritizing “oral feeding safety” for FOIS = 2 vs. “feeding independence” for FOIS = 3–4) (50).
Stroke subtype subgroup	Cortical infarction group, subcortical infarction group	Different infarction locations cause varying degrees of damage to the swallowing neural circuit: cortical infarction primarily impairs the cortical swallowing center, while subcortical infarction affects the cortico-brainstem pathway, which may lead to differences in the regulatory effect of acupuncture (51).
Age subgroup	Young group (18–60 years), Elderly group ( > 60 years)	Elderly patients often exhibit atrophy of swallowing muscles. This anatomical change may result in a slower response to the “neuroregulatory effect” of acupuncture compared to young patients (52).
Baseline NIHSS score subgroup	Mild neurological deficit group (NIHSS ≤ 8), moderate neurological deficit group (NIHSS = 9–16)	Stroke severity is correlated with the prognosis of dysphagia. Patients with moderate neurological deficits may require a higher intensity of intervention to achieve meaningful improvements in swallowing function (53).
Deqi adequacy subgroup (acupuncture group only)	Adequate Deqi group (DQI ≥ 4 and ≥ 2 typical sensations with score ≥ 3), inadequate Deqi group (participants who fail to meet the above criteria)	Deqi is a key link in the efficacy of acupuncture. Adequate Deqi (characterized by typical sensations such as soreness, numbness, distension, and heaviness) may enhance the activation of the swallowing neural circuit, thereby strengthening the therapeutic effect of acupuncture (54).

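### Section 2.12.5 lists the Deqi Index as a confounder for the efficacy models, although it is a post-randomisation response to needling that exists only in the acupuncture arm

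*Protocol article*

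**What the plan says.** Section 2.12.5 names age, sex, duration, baseline NIHSS and FOIS, stroke subtype and comorbidities as potential confounders. It ends the list with the statement that "total treatment expectation scores, and the Deqi Index (DQI), will be accounted for in the analyses". The next sentence reads "For primary and secondary efficacy outcomes, repeated-measures mixed-effects models or multiple linear regression will be employed". Two of the listed items are then sent elsewhere: "Stroke subtypes will be examined using stratified analysis, while comorbidities will be assessed via sensitivity analyses". DQI is not one of them.

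Section 2.8.1, which describes the experimental group, defines the index: "The Deqi Quality Index (DQI) for each participant will be calculated as the mean of the total c-MASS scores recorded at three time points", namely at the start of the intervention and at 15 and 30 minutes. On timing it says "Participants will self-complete the c-MASS within 30 s after each needle manipulation". Section 2.8.2 gives the control group rehabilitation training and describes no needling. Under section 2.7 the allocation envelope is opened once baseline assessments are complete, so any c-MASS score comes after randomisation.

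DQI appears in two more places. Section 2.12.4 compares adequate with inadequate deqi "with the Deqi Quality Index (DQI) included as a covariate in an analysis of covariance (ANCOVA) to assess therapeutic effects". Table 5 in section 2.12.6 has a row labelled "Deqi adequacy subgroup (acupuncture group only", placed under a column whose heading says that the strata are fixed at baseline. Section 2.12.3 separately describes an ANCOVA or mixed model for FOIS, and the only covariate it names is the baseline expectation score.

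**The concern.** A confounder of a treatment comparison must precede treatment. DQI follows allocation, is produced by one of the two treatments, and has no value for patients who are not needled. Adjusting the arm comparison for it conditions on part of what acupuncture does.

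The primary FOIS comparison is at stake. Depending on how controls are coded, the model either cannot estimate the arm effect or estimates a different quantity: the effect of acupuncture in a patient who feels no deqi. Table 5 gives as its rationale that adequate deqi may strengthen the therapeutic effect. The more that premise holds, the more of the effect the adjustment removes.

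**Working it through.** **Inputs from section 2.7.** Mean changes 1.31 and 0.31 (difference 1.00), SD 1.09, margin 0.39, α 0.05 (sidedness not stated), power 0.8, 40 per arm before dropout.

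**The plan's own figure.** n = 2 × (1.645 + 0.842)² × 1.09² / (1.00 − 0.39)² = 39.5, so 40 per arm. Then 40/0.8 = 50 per arm, 100 in total. This reproduces with one-sided α. The two-sided version with the margin needs 51. The unadjusted SE is 1.09 × √(2/40) = 0.2437, and power against the margin is Φ(0.61/0.2437 − 1.645) = 80%.

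**Inputs the documents do not give.** The mean (m) and SD (s) of DQI, and its correlation r with outcome within the acupuncture arm. I write k = m/s and assume k from 1 to 4.

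**Case (a): DQI missing in controls.** A complete-case fit keeps only acupuncture patients. The arm indicator is then constant, and the columns intercept, arm and DQI have rank 2 of 3. The arm effect is not estimable.

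**Case (b): DQI coded 0 in controls.** Let T be the arm indicator (1:1) and DQI = T·X.
- Var(T) = 1/4; Cov(T, DQI) = m/4; Var(DQI) = s²/2 + m²/4.
- Squared correlation = k²/(k² + 2), so variance inflation = 1/(1 − k²/(k² + 2)) = 1 + k²/2.
- The within-arm slope is r × 1.09/s. The arm coefficient is the acupuncture line read at DQI = 0, minus the control mean. It therefore equals the true difference minus (r × 1.09/s) × m = 1.00 − r × 1.09 × k.

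| k (assumed) | Variance inflation | SE | Power vs margin 0.39, one-sided, r = 0 | Coefficient, r = 0.2 | Coefficient, r = 0.3 |
|---|---|---|---|---|---|
| no DQI | 1.0 | 0.24 | 80% | 1.00 | 1.00 |
| 1 | 1.5 | 0.30 | 66% | 0.78 | 0.67 |
| 2 | 3.0 | 0.42 | 42% | 0.56 | 0.35 |
| 3 | 5.5 | 0.57 | 28% | 0.35 | 0.02 |
| 4 | 9.0 | 0.73 | 21% | 0.13 | −0.31 |

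The power column is Φ(0.61/SE − 1.645). Against a zero difference, two-sided, Φ(1.00/SE − 1.96) falls from 98% without DQI to 92%, 66%, 42% and 28% for k = 1 to 4. That is not the planned test and is given for reference only.

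**Simulation check** (4,000 runs, 40 per arm, true difference 1.00, SD 1.09, zero coding). At r = 0.3 the mean coefficient was 0.34, 0.00 and −0.31 for k = 2, 3 and 4, in line with the formula. At r = 0 and k = 3 it was 1.00 with SE 0.59: no bias, only lost precision. With a true difference of zero, k = 2 or 3 and r = 0.3 or 0.5, the mean coefficient ran from −0.65 to −1.64. Zero was then falsely rejected (two-sided, about 0.05) in 34% to 85% of runs, with the mean estimate favouring control.

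**Case (c): DQI centred within the acupuncture arm, 0 in controls.** The coefficient returns to 1.00 with SE 0.23 to 0.24. The article does not specify this coding.

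**Section 2.12.4 against Table 5.** The adequate class requires DQI of at least 4 together with at least two typical sensations rated at least 3. A class comparison that also adjusts for DQI therefore adjusts for part of the class definition.

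**The case against.** The wording of section 2.12.5 is loose. To be accounted for is not the same as entering one model, and stroke subtype and comorbidities show that listed items may be handled in other ways. DQI has its own section, and section 2.12.3 describes the FOIS model without it. A reader might infer that the primary comparison is bound to be lost. The documents do not support that, because they do not settle which model is primary. What remains is that section 2.12.5 expressly covers primary outcomes, diverts only two other items, and nowhere limits the DQI adjustment to the acupuncture arm.

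A reader might also infer that the arm effect must be either not estimable or badly biased. That is too strong. Zero coding with no correlation costs only precision, and within-arm centring avoids the harm. The coding of controls could fairly sit in an unseen analysis plan. Calling DQI a confounder is nevertheless a stated choice, and it is wrong under any coding.

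Two further inferences go beyond the text. DQI alone does not define the deqi classes. The sensation ratings do too, and if the c-MASS total is a sum, two ratings of 3 already give 6, so the threshold of 4 hardly binds. Nor do the documents show the deqi row entering the between-arm forest plot, since that row is marked as acupuncture only.

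The magnitudes are illustrative. At k = 1 the variance inflation is only 1.5.

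**Conclusion.** The point stands in this form: as written, section 2.12.5 places a post-randomisation, one-arm response to treatment among the confounders for the primary and secondary efficacy models. A complete-case fit with DQI missing in controls cannot estimate the arm effect; this follows from the design and needs no assumption. With zero coding, variance inflates by 1.5 to 9 for k of 1 to 4. The estimate moves away from the average arm effect by about r × 1.09 × k, downward if r is positive, as Table 5 presumes. Both k and r are assumptions, so the sizes show what can happen and do not predict what will.

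Sections 2.12.3 and 2.12.5 also leave two primary FOIS models open, which matters in an open-label trial. The class-plus-DQI adjustment in section 2.12.4 and the baseline heading over the deqi row in Table 5 are smaller faults of the same kind. The planned sample size does not depend on this point.

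**What to change.** - Section 2.12.5: delete DQI from the covariate list for every acupuncture-versus-rehabilitation comparison, and adjust only for pre-randomisation covariates, including the stratification factors centre and baseline FOIS.
- Sections 2.12.3 and 2.12.5: state one primary FOIS model with its covariates, and label any other as a sensitivity analysis.
- Section 2.12.4: keep DQI as an exploratory, non-causal analysis within the acupuncture arm (for example, FOIS change on DQI adjusted for baseline FOIS and centre). Use either the binary class or the continuous index, not both.
- Table 5: mark deqi adequacy as post-randomisation, apart from the strata that are fixed at baseline.

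The cost is wording in the protocol or analysis plan, settled before the outcome data are analysed. No data collection changes, and the planned 40 per arm (100 in total) stays as it is.
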